#### Data Collection, Management, and Dissemination

Letters of Information and Consent as well as case report forms will be stored in a locked cabinet in the research office. Each patient will have a unique and study-specific identification code that will be assigned to all aspects of testing. The link between the code and the patient's name will be stored in a secure cabinet in the Primary Investigators' research office. Contact and demographic information (name, telephone number, email, date of birth, date of death, sex/gender, age) will be stored on the secure, password-protected server. FMRI, fNIRS, and EEG data will not have any identifiers within the data and stored using the unique code for each healthy control and patient. A unique web link will be sent to patients who choose to complete longitudinal cognitive assessments using CBS via email which will then be linked back to the patient's study ID. All data will be stored at Western University on a secured and encrypted server that is behind institutional firewalls. The results from the neurocognitive test battery will be stored a secure server at the Brain and Mind Institute. We hope that the results from this study will be presented at both local and international scientific research conferences and will be published peer-revived scientific journals.

The results of this study will be not shared with the clinical team and will not inform patient management. In accordance with our local ethical guidelines, we are not permitted to share the results with the clinical team as this study is at the stage of scientific research rather than clinical practice.

### Follow Up Imaging

Patients will be invited to participate in a follow up imaging session approximately 12 months post-injury to assess for changes in brain responses from acute injury to recovery. Imaging paradigms at the follow up scans will be identical to those used during acute injury.

### Stimuli Paradigms

We will first examine neural activity using passive somatosensory and auditory stimuli. These tasks allow for the assessment of both basic and higher order cognitive processing without the need for overt motor action.

#### Somatosensory Perception Paradigm (fMRI/fNIRS)

Somatosensory stimuli will be administered via electrical median nerve stimulation and will be performed simultaneously with neuroimaging testing with the same clinical parameters used in upper limb somatosensory evoked potentials (36). Electrodes will be placed on a patient's arm while in the fMRI suite using a custom-made high-frequency-shielded cable to a battery-powered nerve stimulator (Nikolet VikingQuest EP stimulator). This same cable will also be used to deliver the stimuli at the bedside when recording with fNIRS. The intensity of stimulation will be delivered at a current to induce a continuous motor threshold (approximately 6–30 mA) and kept constant for each patient. The stimuli will consist of 30-s blocks of stimulation at a rate of 4 Hz with a 0.1 ms pulse duration followed by a 30-s interblock rest period. There will be 8 stimulation and 7 rest blocks, with a total test time of 7 min 30 s per hand. We will assess for basic processing in the primary somatosensory cortex and for higher-order activity in the secondary somatosensory cortex and insula. The extent of somatosensory perception (as indexed by neural responses in the primary and secondary somatosensory cortices, and the insula) may be a predictor of neurological outcome.

#### Auditory Processing Paradigm (fMRI/fNIRS/EEG)

In fMRI and fNIRS, a passive hierarchical auditory task will be administered to assess the auditory processing abilities of patients. A subtraction approach (previously described by Coleman and colleagues (11) will be used to measure 3 levels of processing: (i) sensory (ex. speech vs. silence), (ii) perceptual (ex. speech vs. non-intelligible noise, and (iii) semantic (ex. complex narratives vs. pseudowords). Stimuli will be presented in 30-s blocks in an interleaved fashion and each condition will be repeated 5 times for a total duration of 10 min.

In EEG, we will present three different types of auditory stimuli to elicit event related potentials (ERPs) that reflect different levels of auditory function (37). Specifically, we will compare the EEG responses of individual patients collected during silence (rest), signal correlated noise (SCN) created from word stimuli, and word pairs. Word pairs will either be related (e.g., table-*chair*) or unrelated (e.g., dog—*chair*) to elicit ERP components associated with semantic processing. Basic auditory function will be assessed by contrasting grand-average ERP waveforms during silence (rest) and noise, focusing on the N1-P2 complex. Next, we will compare the amplitude and latency of the N1-P2 components between noise and word trials to index automatic speech discrimination. Finally, we will examine differences in ERP amplitude and latency of the N400 response between related and unrelated word pairs. In healthy individuals, related word pairs typically elicit a higher amplitude N400 response which suggests that semantic congruence—a higher-order cognitive process—modulates this ERP component. Stimuli will be presented in 5 min blocks of 50 trials each, with the total duration of testing being under 30 min. Neural activity in response to this hierarchical set of tasks may be a predictor of clinical outcome; that is to say, patients with activation similar to controls may have a more complete recovery from brain injury than those who will show no, or partial, activation.

#### Covert Awareness Paradigm (fMRI/fNIRS/EEG)

While passive paradigms provide insight into the integrity of higher-order cognitive processing in the brain, these stimuli cannot be used to infer conscious awareness as the auditory and somatosensory paradigms can elicit brain activity without any cooperation on the part of the patient. Here, command following paradigms using mental imagery will be used to assess for covert awareness as they produce specific and well documented patterns of neural activity (10, 19). For fMRI and fNIRS, all participants will be given pre–recorded spoken instructions about how to perform two mental imagery tasks (motor imagery and spatial navigation), which have been described in detail previously (10). For the motor imagery task, participants will be instructed to imagine playing a game of tennis, swinging their arm back and forth to hit a ball repeatedly when cued in the scanner by the instruction “imagine playing tennis”. Patients will be instructed to continue to perform the tennis imagery until they hear the words “now just relax.” Prior to the spatial navigation task, individuals will be instructed to imagine moving from room to room in their home and visualize everything they see when cued with the words “imagine moving around your house”. They will be instructed to continue with the task until they hear the instruction “now just relax.” Both paradigms are five and a half minutes in length and have an interleaved block design of 30 s of mental imagery with alternating rest periods (five blocks of imagery, six blocks of rest).

If patients have reliable and appropriate neural activity to the command following tasks, the same motor imagery paradigms will be used as a communication tool with fNIRS at the patient's bedside at a subsequent testing session within 24 h of when covert command following is detected. The patients could be asked to “Imagine playing tennis” if the answer to a question is “yes” and instructed to “imagine walking through your home” if it is “no”. We will begin with asking questions that have correct and objective answers which may include, “does 1lb weight more than 2 lbs?”, “is your last name < insert incorrect last name>?”, “are you in a hospital?”, and “are you in a supermarket?”. Finally, we will ask questions such as “are you in pain?”, “do you feel safe?” to better understand the patients' perceptions of their surroundings and analyze these responses if the objective and verifiable questions are answered correctly.

The lower spatial resolution of EEG requires a slight modification of the mental imagery tasks. In EEG, patients will be asked to imagine squeezing their right hand or moving their toes on both feet each time they hear a beep (19). We will present 15 beeps in a single block and all blocks will end with instructions for the patient to relax. This will be repeated for four to eight blocks total, with hand and toe instructions presented in a random order. This task will last approximately 30 min.

#### Movie Paradigm (fMRI/fNIRS/EEG)

An audio clip from the movie *Taken* will be presented (20, 38). During movie narratives, neural activity synchronizes in sensory regions, coding its perceptual properties, as well as in frontoparietal areas that are associated with the executive processes required to follow a plot. The latter can be used to infer a similar experience (or executive processing) across healthy individuals and can be extended to detect covert cognition in patients who remain behaviorally non-responsive. A “scrambled” version of the audio will also be played that will serve as an auditory control condition. The movie paradigm will be approximately 10 minutes in length. Synchronization of the frontal and parietal cortices to the movie narrative task may be a predictor of neurological outcome.

#### Resting State Paradigm (fMRI/fNIRS/EEG)

A resting-state scan will be acquired to image the brain's intrinsic functional connectivity at rest in the absence of any external stimuli. The resting state scan will be 6 min in length. The extent of functional connections that are preserved in acute brain injury may be a predictor of neurological outcome.

### FMRI Procedures

Participants will be accompanied by a nurse and respiratory technologist during the MRI scanning. The total time of the study will be approximately 60 min. Participants may be removed from the MRI for breaks at any time if necessary. During imaging, patients will be closely monitored by the treating medical team. A total of 6 research scans will be acquired. Imaging data will be acquired on either a 1.5T General Electric MRI machine or a 3T Siemen's scanner located at London Health Sciences Centre (London, Canada). Whole-brain anatomical 3D-SPGR T1-weighted images and functional scan parameters may vary based on the scanner used for imaging.

#### FMRI Data Analysis

fMRI data will be preprocessed and analyzed using Statistical Parametric Mapping (SPM) (http://www.fil.ion.ucl.ac.uk/spm). For the passive paradigms (somatosensory and auditory) as well as the command follow tasks, the analyses will be based on the general linear model (GLM) using the canonical hemodynamic response function. A GLM will be created with regressors for each condition in each active or passive paradigm. Six individual motion parameters will be included as covariates to account for variations due to movement. Healthy control data will be used to generate regions of interest (ROI) masks using a threshold of *p* <0.05, family-wise error corrected. The ROIs will be created using the SPM compatible MarsBaR software (http://marsbar.sourceforge.net/). The statistical threshold to detect neural activity may vary based on the task with supporting evidence from previous literature (10, 11). To assess resting-state functional connectivity, an independent component analysis will be used to decompose the resting state BOLD signal into 20 statistically independent spatial and temporal components with the GIFT software package (http://icatb.sourceforge.net). Components will then be spatially correlated to 10 resting state network templates derived from the BrainMap database (39).

### EEG Procedures

Patients will be fitted with a 128-sensor saline electrolyte electrode cap, from Electrical Geodesics Inc. (EGI). Fitting the cap and checking impedances (below 50 Kohms) will take approximately 15 min. The total time of the testing will be approximately 60 min.

#### EEG Data Analysis

EEG data will be band passed and notch filtered (notch at 60 Hz) and artifacts will be removed using a combination of visual inspection (i.e., of trial epochs), automatic channel rejection, and independent components analysis (ICA). We will examine passive auditory processing using standard ERP analysis techniques (40). These will involve testing the differences in grand average ERP amplitude and latency between silence vs. sound (N1-P2 complex), sound vs. words (modulated N1-P2 or P3), and unassociated word pairs vs. associated word pairs (N400). We will use a correlated components analysis to calculate inter-subject correlations (ISCs) between individual patients and controls during the movie task to assess narrative processing (20). Command following ability will be determined by quantifying systematic decreases in mu (7.5–12.5 Hz) and beta (13–30 Hz) power in scalp regions over the lateral premotor (hand) and medial premotor (toes) cortex (19). For resting state EEG, we will compute inter-electrode magnitude square coherence to examine the functional connectivity profiles of individual patients (41).

### FNIRS Procedures

The fNIRS data will be collected with a high-density NIRScout system consisting of 32 sources and 32 detectors (NIRx Medical Technologies). Laser diodes emitting light at four wavelengths (λ = 785, 808, 830 and 850 nm) will be used to measure changes in regional concentrations of oxy- and deoxy-hemoglobin. The sources and detectors will be attached to the head in two bilateral grids with optodes extending from the frontal lobe to the parietal areas. A high-density setup will be used around the primary auditory cortices to enhance the spatial resolution around the superior temporal gyri and around the primary somatosensory cortices in the parietal regions (see Figure 2). Eight short source-detector separations (8 mm) connected to the last detector will be used to monitor scalp effects, while channels with larger source-detector distances (3–4 cm) will measure changes from the brain.

**Figure 2 F2:**
[figure not shown]
FNIRS montage used in this study. The red circles represent the sources (32 in total) while the blue circles represent the detectors (31 in total). The blue circles around sources 2, 8, 13, 16, 18, 23, 28, 31 represent the location of the short channels which are connected to the last detector (detector 32).

#### FNIRS Data Analysis

The data will be preprocessed and analyzed using MATLAB and freely available software packages such as NIRS Toolbox and Homer2. Each time series will be filtered to eliminate the effects of physiological changes such as heart rate and breathing, corrected for motion artifacts and short-channels will be regressed from the longer channels to reduce scalp contributions (42). For the sensory processing and command following tasks, the time courses will be fitted to the general linear model to detect significant hemoglobin changes. A channel will be considered activated if there is a significant increase in oxyhemoglobin and a concurrent significant decrease in deoxyhemoglobin. Network analysis will be performed for the resting state analysis (43). Pearson correlation coefficient (*r*) between the time-courses of two channels for all possible combinations will be computed, and these will be considered linked if the *r* is above a predetermined threshold. Graph theory will also be used to extract global network parameters to characterize the network.

### Statistical Analysis

To establish whether fMRI can aid prognostication in acute disorders of consciousness, imaging results will be related to long term behavioral and cognitive follow up assessments. For the somatosensory and auditory processing task, the Spearman's rank-order correlation coefficient will be used to measure the rank correlation between the extent of acute sensory processing and a patient's behavioral scores at 3-, 6-, and 12-months post- injury, as indexed by the GOS-E. This same method will be used to evaluate the relationship between the degree of acute functional connectivity, as measured by the correlation value to healthy controls, to long term outcome. For the movie narrative, the correlation between individual patients and the healthy control group during the intact clip will be related to long term outcome. The primary outcome will be 12 months post injury, and the secondary outcomes will be at 3 and 6 months. Linear regressions will be performed to investigate the effect of clinical and demographic variables on acute imaging features and patient outcomes. All statistical tests will be corrected for multiple comparisons using a False Discovery Rate. We will also determine the sensitivity, specificity, positive predictive value, and negative predictive value for the imaging procedures outlined in the protocol.

Receiver operating characteristic (ROC) and area under the curve (AUC) analyses will be generated to identify a cut-off value differentiating conscious from unconscious patients, as well as patients who are to have a good or poor outcome for each paradigm. Outcome predictors (as assessed by the area under a receiver operating characteristic curve) will be compared between acute neuroimaging findings and traditional prognostic markers (such as EEG reactivity, pupillary reflexes, brainstem reflexes, serum biomarkers, evoked potential results) to assess whether functional neuroimaging responses are more accurate. We will account for patient's age, gender, days since injury, down time (for cardiac arrest patients), MODS and SOFA score, as covariates during the statistical analyses. Where possible, patients will be grouped by etiology in the statistical analyses. In line with the previous investigational neuroimaging literature, we will characterize a “good” outcome as a recovery that allows for sufficient function for independent activities of daily life (3, 18, 44), whereas a “poor” outcome will be defined as a severe disability that impacts all aspects of daily living, a coma, vegetative state/unresponsive wakefulness syndrome, and death. In respect to the GOS-E, a “good” outcome is characterized as a score of 4 or greater, signifying the ability to be left alone for up to 8 h during the day without assistance (8).

To establish whether fMRI measures of covert awareness can be used in the diagnosis of acute disorders of consciousness in the ICU, we will seek to ascertain the proportion of patients who show signs of covert awareness, in the form of plot and command following, and subsequently the proportion of those participants who can use mental imagery tasks as a means of communication. A variety of statistical measures will be used, where appropriate, to determine whether neural activity differs between prognostic groups (i.e., survivors vs. non survivors; good outcome vs. poor outcome). Machine learning models will also be applied to evaluate neuroimaging measures as predictors of covert consciousness and subsequent recovery. Features will be extracted from each imaging modality and a two-class linear classifier (such as support vector machines) will be used to classify patients as survivors and non survivors. Patient outcome 12-months post injury will be used as ground truth while training the classifier. Features such as the median change in the signal during the task period and the correlation coefficient between the time series and the theoretical activation model (i.e., box function convolved with a hemodynamic response) will be extracted from the time courses obtained from task-based stimuli. For the resting state task, previous work has shown that the frontoparietal network and the default mode network are critical for consciousness, therefore, the strength of the correlation between channels in these networks will be used to supplement the features extracted from the active tasks. In addition to supervised machine learning, the feasibility of deep learning to predict outcome will also be assessed. The main advantage of deep learning is the ability to extract features that could be overlooked by the user. Given the breadth of data, deep learning approaches such as the convolutional, feedforward, and artificial neural network may be beneficial (45). These options will be further explored once enough data is collected to make this type of analysis feasible. Finally, a feature ranking approach may be used to quantify the importance of each method and metric.

Given that fMRI and fNIRS rely on BOLD imaging principles, we will examine fNIRS results against fMRI findings to assess the accuracy of fNIRS to detect brain activity during various tasks at the bedside. For the tasked based paradigms, ROI will be identified from the fMRI results and the fNIRS channels corresponding to those areas to determine the presence of significant changes in oxy- and deoxyhemoglobin. For the resting state task, the strength of the correlation across functional networks of interest (i.e., frontoparietal network, default mode network) will be compared (15, 17). Furthermore, given that two MRI scanners with different field strengths will be used in this protocol, we will analyze data on the 3T and 1.5T as separate cohorts of patients based on which MRI scanner the data was obtained from. We also plan to address how this will impact the data by running research scans on both scanners in the same group of healthy volunteers. Finally, investigators will be blinded when analyzing predictive data and the study coordinator will be blinded from the acute imaging results when collecting outcome measures.

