## Abstract

Multi-modal neuroimaging techniques have the potential to dramatically improve the diagnosis of the level consciousness and prognostication of neurological outcome for patients with severe brain injury in the intensive care unit (ICU). This protocol describes a study that will utilize functional Magnetic Resonance Imaging (fMRI), electroencephalography (EEG), and functional Near Infrared Spectroscopy (fNIRS) to measure and map the brain activity of acute critically ill patients. Our goal is to investigate whether these modalities can provide objective and quantifiable indicators of good neurological outcome and reliably detect conscious awareness. To this end, we will conduct a prospective longitudinal cohort study to validate the prognostic and diagnostic utility of neuroimaging techniques in the ICU. We will recruit 350 individuals from two ICUs over the course of 7 years. Participants will undergo fMRI, EEG, and fNIRS testing several times over the first 10 days of care to assess for residual cognitive function and evidence of covert awareness. Patients who regain behavioral awareness will be asked to complete web-based neurocognitive tests for 1 year, as well as return for follow up neuroimaging to determine which acute imaging features are most predictive of cognitive and functional recovery. Ultimately, multi-modal neuroimaging techniques may improve the clinical assessments of patients' level of consciousness, aid in the prediction of outcome, and facilitate efforts to find interventional methods that improve recovery and quality of life.

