#### Feasibility

The sample size for this study was determined based on feasibility. We accounted for the estimated ICU survival rates for various common severe brain injuries, loss of data due to poor quality (~5–10%), and the potential of withdrawal from study procedures before, during, or after testing commences for various reasons (patient regains awareness before imaging procedures are complete, decline of reconsent, unexpected medical complications). Based on admission information obtained from support services at London Health Sciences Centre, we can expect approximately 550–650 patients admitted into the ICU with a life threating brain injury that requires mechanical ventilation each year. To this end, over 7 years we can expect approximately 4,200 patients that may be eligible for this study. As such, we are confident that 350 patients is an appropriate and feasible number for this study. Furthermore, this project will have a fulltime research coordinator who will work closely with the bedside nurses and attending physicians to schedule and ensure testing takes place at the correct and appropriate time. The research coordinator will also schedule and administer follow-up cognitive testing and telephone questionnaires.

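### Sensitivity, specificity, PPV and NPV taken at cut-offs searched in the study's only patient cohort are apparent values, biased upward, yet the abstract calls the study a validation

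*Protocol article*

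**What the plan says.** Under Statistical Analysis, the article plans ROC and AUC analyses "to identify a cut-off value differentiating conscious from unconscious patients". It plans the same for good versus poor outcome, paradigm by paradigm. The same section states: "We will also determine the sensitivity, specificity, positive predictive value, and negative predictive value for the imaging procedures outlined in the protocol". It later describes a two-class linear classifier trained on 12-month outcome, and a list of covariates to be accounted for.

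The Abstract gives the aim as to "validate the prognostic and diagnostic utility of neuroimaging techniques in the ICU" and the sample as one cohort: "We will recruit 350 individuals from two ICUs over the course of 7 years". The healthy controls (up to 50) serve as a reference for typical activity and are not a test sample. For MRI, "we will analyze data on the 3T and 1.5T as separate cohorts of patients". Grouping by etiology is planned where possible. A False Discovery Rate correction and blinding of the analysts are stated. No pre-fixed ROC cut-off, hold-out set, cross-validation or bootstrap correction is named.

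**The concern.** A cut-off chosen because it performs best in a set of patients will look better in those patients than in the next ones, since the search also fits the sampling noise. Scoring it in the patients who produced it is derivation. A reader of the abstract would take the resulting sensitivity and specificity as validated performance. The Discussion expects the results to inform future prognostic and diagnostic guidelines, so inflated figures could carry into that use.

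The stated safeguards do not help. False Discovery Rate control acts on significance tests, not on accuracy estimates. Blinding does not remove optimism. The two scanner cohorts are analysed separately, and neither is used to test cut-offs found in the other. The Discussion raises the difficulty of finding true sensitivity and specificity, but only because of withdrawal of life-sustaining measures.

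**Working it through.** **Plan's own figures.** The Feasibility section gives "approximately 550–650 patients admitted into the ICU" per year and says "over 7 years we can expect approximately 4,200 patients that may be eligible for this study". Check: 7 × 550 = 3,850, 7 × 600 = 4,200 and 7 × 650 = 4,550, so the midpoint reproduces 4,200. The 350 has no formula behind it ("The sample size for this study was determined based on feasibility"), and no target AUC, sensitivity or precision is given. With the stated 10% upper figure for data loss, 350 × 0.90 = 315.

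**Assumptions not in the documents.** Binormal marker with equal variances; cut-off chosen to maximise the Youden index J = Se + Sp − 1; true AUC 0.70; 30% or 40% positives; n per ROC curve as shown.

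**Formulae.** Negatives follow N(0,1) and positives N(d,1), with d = √2·Φ⁻¹(AUC) = √2 × 0.524 = 0.742. At cut-off t, true Se = 1 − Φ(t − d) and true Sp = Φ(t). The best J any cut-off can reach is 2Φ(d/2) − 1 = 2Φ(0.371) − 1 = 0.289. In each simulated sample the best cut-off is found, scored in the same sample (apparent), and scored with the formulae (true).

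**Result, 30% positives:**

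| n | apparent Se / Sp | true Se / Sp | excess in Se+Sp (points) |
|---|---|---|---|
| 315 | 0.672 / 0.660 | 0.631 / 0.646 | 5.5 |
| 175 | 0.685 / 0.664 | 0.627 / 0.645 | 7.7 |
| 100 | 0.698 / 0.670 | 0.619 / 0.648 | 10.2 |
| 50 | 0.732 / 0.678 | 0.616 / 0.643 | 15.0 |

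(Excesses were computed before rounding.) At n=315, PPV is 2.8 points and NPV 2.1 points too high. The apparent J there, 0.672 + 0.660 − 1 = 0.332, exceeds the 0.289 that the best possible cut-off could achieve. The n=175 row would be an equal scanner split of 350, which is an assumption.

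**Result, 40% positives:** apparent v true J is 0.33 v 0.28 (n=300), 0.36 v 0.27 (n=100) and 0.40 v 0.26 (n=50).

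**Sensitivity to the assumptions.** Over AUC 0.7–0.9 and 15–50% positives, the excess is 3.0–7.5 points at n=315–350 and 10.2–19.4 at n=50. It is upward in every case.

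**Does correction work?** In a separate run at 30% positives, with the search repeated inside 10-fold cross-validation:

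| n | apparent J | cross-validated J | true J |
|---|---|---|---|
| 315 | 0.330 | 0.277 | 0.278 |
| 100 | 0.370 | 0.262 | 0.267 |
| 50 | 0.413 | 0.258 | 0.257 |

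Nearly all the excess disappears.

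**Fitted models.** The AUC of one unfitted marker uses no cut-off, so the search leaves it alone. It is inflated once coefficients are estimated. The article lists six covariates (age, gender, days since injury, down time, MODS, SOFA). A marker plus these six, all pure noise and fitted as one model with 40% positives, shows a mean apparent AUC of about 0.58 (n=315), 0.65 (n=100) and 0.71 (n=50) against a true 0.50. Down time applies only to cardiac arrest patients, so some models would have fewer terms.

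**The case against.** **A condensed article may leave resampling to a fuller plan.** This is the strongest counter-argument: naming ROC analysis excludes no internal validation. It stands to this extent: the conclusion is about the method as published. However, the article states the search, the accuracy outputs and the validation claim together, and followed as written these do not fit.

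**The accuracy measures are not expressly tied to the searched cut-offs.** This stands. The article also gives activation rules that do not use outcome: control-derived regions and literature-supported thresholds for fMRI, and a joint oxy-/deoxyhemoglobin criterion for fNIRS. Accuracy at those rules carries no search bias, so it would be wrong to infer that every reported sensitivity or specificity is inflated.

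**A reader might infer that imaging could beat traditional markers through the cut-off search alone.** The documents do not support this. The comparison is made by AUC, which does not depend on a cut-off for a single marker.

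**A reader might infer that the best paradigm is picked by AUC.** No such ranking is stated. The only ranking mentioned is an optional feature ranking following the machine-learning plans. The section headings give 2 + 3 + 3 + 3 + 3 = 14 paradigm-by-modality pairs, but no rule selects among them.

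**A reader might infer that every cut-off rests on a small subset.** The scanner split concerns MRI data, not EEG or fNIRS, and etiology grouping is conditional.

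**The bias is modest at full size.** With 120 positives, 180 negatives and Se and Sp near 0.65, the standard error of J is √(0.65 × 0.35/120 + 0.65 × 0.35/180) = 0.056, so a 5-point excess is about one standard error. That is correct. But bias shifts every such estimate the same way, and an uncorrected interval would be centred too high.

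**The numbered objectives speak of establishing, developing and exploring.** The validation wording is confined to the abstract, so that part is a matter of description.

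**Conclusion.** The concern holds for a defined set of results: sensitivity, specificity, PPV and NPV at ROC-derived cut-offs, and the accuracy or AUC of the trained classifier or any covariate-fitted or combined model. As the method is published, these are apparent values with a known upward bias, and they do not amount to the validation claimed in the abstract.

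At true AUC 0.70 with 30–40% positives, the excess in Se+Sp is about 5 points when nearly all patients enter one analysis, about 10 at n=100 and about 15 at n=50. The last two matter only if small scanner or etiology subsets get their own cut-offs, and the article gives no subset sizes. All sizes depend on the assumed binormal marker, Youden criterion, AUC and prevalence; the direction did not change anywhere in the range tried.

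The Spearman correlations with GOS-E, the AUC of a single unfitted marker, and accuracy at activation rules fixed without reference to outcome are unaffected. This should be corrected, but it does not undermine the study as a whole.

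**What to change.** Add to Statistical Analysis:

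- State which positivity rule (ROC-derived cut-off or fixed activation rule) each sensitivity, specificity, PPV and NPV refers to.
- Report measures at ROC-derived cut-offs, and the AUC or accuracy of any fitted model or classifier, after bootstrap optimism correction or nested cross-validation. Repeat the cut-off search and all model fitting inside each resample. Alternatively, lock cut-offs on earlier recruits and test them on later ones.
- Give confidence intervals for the corrected values.
- In the Abstract, describe the aim as to develop and internally validate the markers.

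The cost is a few sentences and some computing, with no new patients or procedures. Reported accuracy will be slightly lower. The temporal hold-out would also leave fewer patients for each step, so resampling is the better default where scanner or etiology subsets are analysed.
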